### Sample size

We conducted a pilot two-arm randomised controlled trial at four facilities, whereby eight haemodialysis patients were assigned randomly into either of the two groups: Group 1 listened to Mozart, and Group 2 listened to the news on the radio. The primary outcome was cannulation pain evaluated via a VAS. A previous review suggested that patients who record a baseline VAS score of more than 30 mm might indicate at least moderate pain [65]. Moura and colleagues reported that 20% of the haemodialysis patients suffer from pain, indicated by a VAS pain score of more than 30 mm [4]. In our pilot study, the mean VAS results were 20.5 mm in Group 1 and 25.4 mm in Group 2. All VAS scores were normally distributed, and the standard deviation was 12.0 mm. Based on results of clinical trials of analgesic agents [66, 67] and a cost-benefit performance of music therapy, a difference of 4.9 mm was considered to be clinically significant and was used for the sample size design. From these results, we computed that 95 patients are needed to observe a treatment effect based on this effect size at a power of 80% with a two-sided significance level of 5%. Assuming participant attrition, we will recruit a total of 120 participants. As the proposed study is a crossover trial wherein the statistical power is assumed to be greater than that of a two-arm design, we believe that our study is adequately powered.

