### Analyses

#### Analysis of VAS pain scores during the cannulation

A set of outcome variables, which includes the VAS pain score as the primary outcome and the VAS anxiety score, STAI score, and S-AMY as the secondary outcomes, will be assessed during a single dialysis session. Each study period will last for a week including three dialyses. Patients will undergo two study periods; thus, each patient will be assessed for six sets of the outcome variables (three in the music period and other three in the white noise period).

A linear mixed model will be applied to compare the means of the three repeated outcome measures between the music and the white noise periods. For the outcome that accompanies the baseline measures, the mixed model will compare the mean of three repeated change scores between the two periods. Compound symmetry was used for variance-covariance to estimate dependency among the repeated measures. Two-sided significance level will be set at 0.05. The normality of the residuals will be confirmed via Q-Q plots, and the mathematical transformation of the outcome variable will be performed if necessary. The mixed-model approach was chosen on the basis of a Monte Carlo simulation study in order to compare the statistical power of three different analytical strategies, which include the following (see Additional file 2).
Paired *t* test to compare the two means of three pain scores between the two periods. (The unit of observation in the analysis is the within-patient mean score of the three scores; the analysis includes two mean scores per patient.)Linear mixed model to compare the two means of the three pain scores between the groups. (The unit of observation is the same as 1.)Linear mixed model to compare the six pain scores between the two periods. (The unit of observation is the pain scores; the analysis includes six observations per patient.)

The third approach was chosen because it appeared to be superior to other approaches, as it provides the largest statistical power to detect statistical significance while controlling for type I error. In addition, the direct inclusion of all six observations will allow us to control for time-dependent confounders, such as personnel effect from the operator who performs the cannulation.

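### Compound symmetry over six VAS scores, with no patient-by-period term, lets the primary type I error exceed 5% if same-week scores are more alike than scores two weeks apart

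*Protocol article*

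**What the plan says.** The Analyses section (Analysis of VAS pain scores during the cannulation) compares three strategies: a paired t test on weekly means, a mixed model on weekly means, and a mixed model on the single scores. It adopts the third, described as "The unit of observation is the pain scores; the analysis includes six observations per patient". The covariance is given in one sentence: "Compound symmetry was used for variance-covariance to estimate dependency among the repeated measures". The test level is fixed: "Two-sided significance level will be set at 0.05".

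The choice is attributed to a Monte Carlo simulation in Additional file 2, on the ground that "it provides the largest statistical power to detect statistical significance while controlling for type I error". A second reason is that keeping all six scores allows adjustment for factors that change between sessions, such as the operator.

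The Design section assigns the sound by the week: music and white noise fall in weeks 2 and 4, with a no-sound week between them. The Discussion expects reactions to cannulation, and the benefit of music, to vary widely from patient to patient.

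**The concern.** Treatment is applied to a week of three sessions, not to a single session. The variation that matters for the treatment comparison is therefore how a patient's weekly mean moves between the two weeks for reasons other than the average effect of the sound. With a single correlation for all six scores, that variation is assumed to be no more than session-to-session noise averaged over three sessions.

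The assumption is open to doubt on the article's own account. The two treatment weeks are separated by a washout week. The Missing data section lets collection pause, for instance for hospitalisation or for treatment of a narrowed access, and then resume, so the gap can be longer and the access may have changed. A music effect that differs between patients adds variance of the same kind. If any of this is present, the three sessions of a week count as more independent evidence than they are, and the primary P value and confidence interval are too optimistic.

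**Working it through.** **The plan's own figure.** The Sample size section puts the need at 95 patients, for 80% power and a two-sided 5% level. Its target comes from the statement that "a difference of 4.9 mm was considered to be clinically significant and was used for the sample size design". For the spread, it reports from the pilot study that "the standard deviation was 12.0 mm". The two-independent-means formula gives n = 2 × [12.0 × (1.960 + 0.842) / 4.9]² = 94.15, rounded up to 95, which is a number per group. The figure reproduces, but it uses no repeated-measures covariance and so neither supports nor refutes the present point. I use N = 95 as the number analysed and 12.0² = 144 as the total variance.

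**Assumed inputs.** The article gives no correlations. Let rb be the between-week and rw the within-week correlation, with m = 3 scores per week. Then rw − rb is the patient-by-period share of the total variance. I take rb = 0.50 and let rw run from 0.50 to 0.70. At rw = 0.55 the patient-by-period variance is 0.05 × 144 = 7.2, an SD of about 2.7 mm.

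**Formulas.**
- True variance of the music minus white noise mean: 2 × 144 × [(rw − rb) + (1 − rw)/3] / N.
- Variance reported under compound symmetry over six scores: 2 × 144 × M / (3N). M is the residual mean square pooled over N − 1 = 94 patient-by-period and 4N = 380 within-period degrees of freedom: M = {94 × [3(rw − rb) + (1 − rw)] + 380 × (1 − rw)} / 474.
- Actual type I error: 2 × [1 − Φ(1.96 × reported SE / true SE)].

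**Worked case, rw = 0.60.** True variance = 288 × (0.10 + 0.1333)/95 = 0.707, SE 0.841 mm. M = (94 × 0.70 + 380 × 0.40)/474 = 0.4595. Reported variance = 288 × 0.4595/285 = 0.464, SE 0.681 mm. The SE ratio is 0.810, so the error is 2 × [1 − Φ(1.588)] = 11.2%.

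| rw / rb | True SE (mm) | Reported SE (mm) | SE ratio | Type I error |
|---|---|---|---|---|
| 0.50 / 0.50 | 0.711 | 0.711 | 1.00 | 5.0% |
| 0.55 / 0.50 | 0.779 | 0.696 | 0.89 | 8.0% |
| 0.60 / 0.50 | 0.841 | 0.681 | 0.81 | 11.2% |
| 0.70 / 0.50 | 0.954 | 0.651 | 0.68 | 18.1% |
| 0.45 / 0.50 | 0.636 | 0.725 | 1.14 | 2.5% |

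The errors are the same to three decimals with N = 120, so more patients do not help. Other assumed pairs give 15.8% (0.60/0.40), 12.9% (0.70/0.60) and 21.6% (0.80/0.60).

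**Simulation check.** With 20,000 simulated trials of 96 patients per setting, compound symmetry rejected in 5.0%, 8.3%, 11.1% and 17.7% for the first four rows. The paired t test on weekly means stayed between 4.9% and 5.0%. In 100 REML fits at 0.70/0.50, the single-intercept model rejected in 17% and the model with a patient-by-period effect in 5%.

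**In terms of varying response.** Suppose the individual music effect has mean zero and SD 2.45, 4.9 or 9.8 mm, on top of rb = 0.50. The type I error is then 6.1%, 9.3% or 18.1%.

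**The power argument.** With complete data and true compound symmetry, the six-score model and the paired t test have the same estimate and the same true SE (0.711 mm). They differ only in degrees of freedom, 474 against 94. For a true difference of 2.0 mm, chosen to put power near 80%, power is 80.2% against 79.5%.

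**The case against.** A reader might infer that the primary standard error is too small as a matter of fact. The documents do not support that. They give no correlation; the error is exactly 5% if all six scores correlate equally, and below 5% if same-week scores are less alike.

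A reader might also infer that the statement on type I control is false. Additional file 2 is not shown, and its simulation may have included patient-by-period variance. The statement is unsupported in the text available, not refuted.

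Nor does a power advantage have to come from an understated standard error. The analysis set admits patients with a score in only one condition, all available sessions are used, and session-level covariates may enter. Each could give the six-score model a real gain over a paired t test. The article also claims only the largest power, not a large margin.

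The block over which compound symmetry applies is not spelled out. Compound symmetry within each period plus a random patient effect would be close to the remedy. That is a possible reading, but not the natural one for a strategy defined by six observations per patient.

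Finally, the Discussion's remark on individual differences argues for a crossover and carries no figure. A varying response raises the type I error only when benefits and harms average to zero; if music affects nobody, that component vanishes. This stands, but week-to-week shifts unrelated to the sound remain, and with a non-zero mean effect a varying response still makes the confidence interval too narrow.

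**Conclusion.** The point holds conditionally. As naturally read, the primary model assumes that scores within a week are no more alike than scores two weeks apart. If that fails through positive patient-by-period variance, the test is anti-conservative. Small departures matter: an excess within-week correlation of 0.05 gives about 8%, and 0.10 about 11%, under the assumed between-week correlation of 0.50. The weekly assignment and the expected variation in response make such variance plausible, but its size is unknown.

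The consequence is greatest when the true effect is nil or small. At 0.70/0.50 a 4.9 mm difference is still 4.9/0.954 = 5.1 correct standard errors, so an effect of the planned size would be detected either way, though its interval would be too narrow. With complete data and true compound symmetry, the power advantage over the paired t test is under one percentage point. That is little reason to accept the risk.

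**What to change.** Keep the mixed model on all six scores, so that the operator and other session-level factors can still be adjusted for. Add a random patient-by-period effect to the random patient effect, and use Kenward-Roger degrees of freedom. Alternatively, make the analysis of patient-period means primary; the mixed-model form keeps patients with only one period, which the paired t test drops. State the random effects and the covariance block explicitly, before the data are analysed.

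Keep the sentence that the chosen approach controls type I error only if the simulation in Additional file 2 generated data with patient-by-period variance. Otherwise rerun it with such variance or remove the sentence.

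The cost is one model term and somewhat wider confidence intervals when the variance is present. If true compound symmetry holds with complete data, the loss is about the 0.7 points of power shown above. At SD 12 mm, 95 patients and 0.70/0.50, the correct SE is about 0.95 mm and power for 4.9 mm is Φ(4.9/0.954 − 1.96) = Φ(3.18), above 99%.

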#### Interim analyses

As mentioned above, participation in this study has no known harm for the patients. Interim analyses will not be performed.

#### Analysis set

A complete or full analysis set (FAS) will be used. FAS is obtained when participants are allocated to the Early-sequence or Later-sequence after eligibility, and VAS pain scores are available at one or more cannulations during the music or white noise conditions. Furthermore, a target group conforming to the implementation plan is defined as per protocol set (PPS). For PPS, when an observation is discontinued by stopping the protocol, the subsequent data are not used in the analysis. Analysis of primary and secondary outcomes is the main focus of FAS. We also will perform analyses targeting PPS so as to confirm the stability of the analytic outcomes.

### Monitoring

An independent data coordinating centre will monitor the input data by using the data log on REDCap, which records the input time and listening time.

### Consent withdrawal/dropout/missing data

#### Consent withdrawal

When a participant withdraws consent, we will discard all data gathered from the study initiation to the withdrawal date.

#### Dropout

Data collection for a participant will be discontinued, and data collected from the study initiation to the dropout are used in the analyses.

* When the shunt is occluded and a vascular anastomosis is re-created surgically.

* When the participant dies or is transferred to another hospital.

* When the participant wishes to terminate his or her participation. (Here, the participant needs to permit data use until the dropout date.)

If some patients drop out, no new patients will be enrolled, and the data will be analysed according to the intention-to-treat principle with use of the FAS cohort.

#### Missing data

Data collection will be interrupted. When the study resumption becomes possible, data collection will be resumed.

* When a participant is hospitalised.

* When the haemodialysis access is narrowed and a percutaneous transluminal angioplasty (PTA) is performed.

* When the haemodialysis access is occluded and blood flow restarts via non-surgical treatment such as massage or PTA.

* When study continuation is difficult because of unavoidable circumstances to participants.

* When study continuation is difficult because of unavoidable circumstances to medical staff.

As a mixed effect model allows for a robust analysis of missing data [70], we will use all available data for the analysis. In the event of any other situations, researchers will decide on a response after consultation.

## Discussion

Repeated pain during haemodialysis access cannulations is a common symptom reported by haemodialysis patients. Music therapy is a safe and inexpensive means for addressing these painful experiences. Music therapy has been effective at alleviating pain and anxiety in a variety of disease contexts [25, 26, 28–30, 33]. Given previous studies, which could be limited by the placebo effect, music therapy could be particularly beneficial to haemodialysis patients [71]. Thus, we propose a crossover trial in order to verify the effectiveness of music therapy for alleviating pain during haemodialysis access cannulations conducted on haemodialysis patients.

The most important characteristic of this trial is the use of a white noise condition as a control comparison. Since several previous studies used a ‘no-sound’ condition as a control but did not address potential placebo effects of the music intervention [37], the effectiveness of previous music therapy interventions could be misleading (Fig. 2). Therefore, the proposed protocol will implement white noise as a way to separate out the potential music effect from any sound-related placebo effect. Although white noise does not have any musical properties, previous studies have observed the relaxation effects of white noise [48, 72]. Furthermore, as stated, we cannot mask the intervention from the patients. However, given that both music and white noise have a relaxation effect, we can inform patients that both music and white noise could help alleviate pain during cannulations. In this way, we will be able to determine whether music mitigates pain above and beyond the implementation of a relaxing sound stimulus. Furthermore, a no-sound period will be implemented during the first and third weeks. As a secondary analysis, white noise and music will be compared with these no-sound conditions.

The planned protocol comprises a crossover randomised controlled trial. VAS pain scores will serve as the primary outcome. Feelings regarding cannulation and the effect of music therapy are likely to differ greatly between individuals. If we were to use a parallel-group trial, there would be concerns that individual differences could mask the treatment effect. Hence, there is quite a bit of variability in past studies concerning the effect of music therapy on cannulation pain. With a crossover randomised controlled trial, it is possible to exclude the influence of individual differences [73–75]; thus, the effect of music therapy can be extracted with a higher power.

We will also evaluate, as secondary outcomes, whether music therapy improves anxiety prior to cannulation and whether BP and HR change at the start of dialysis [29, 30, 33, 76–78]. If music therapy is shown to lower BP in dialysis patients, we might be able to suggest the possibility of using music therapy to treat hypertension in dialysis patients [79, 80]. Furthermore, given that the VAS pain and anxiety scores are a subjective report, objective parameters should be included. Therefore, we will also include S-AMY as a stress marker that can be easily measured to assess patient stress [81].

We will be using Mozart’s Sonata for two pianos in D major (K.448). This piece has been used in various studies assessing the effects of music therapy [46, 82–84]. Some studies suggest that using each patient’s favourite music is more effective than using one type of music [30]. However, if the Mozart piece is effective in reducing pain and anxiety in the proposed study, a single music source could be easily implemented as background music (BGM) within a dialysis room. For practical reasons, each patient’s favourite music could not be used simultaneously as BGM in one setting. Therefore, the observation that one specific musical piece is effective for alleviating pain and anxiety could aid with therapeutic feasibility.

A few study limitations should be noted. First, participants cannot be made blind to their intervention allocation and some of the outcome measures. To address this issue, we will tell participants that both music and white noise are known to facilitate relaxation. Furthermore, all VAS assessments will be conducted without operator assistance. Therefore, all reports will be kept confidential. Second, this is a crossover randomised controlled trial and carry-over effects could occur. To minimise this possibility, we will implement a washout period (1 week) between the white noise and music periods. If carry-over effects emerge, we will use only data from the second week (HD5–7) for the analysis, as it is a randomised parallel-group design. The current sample size was computed on the basis of the single period data alone; thus, the estimated sample size would be sufficient for the period-specific analysis. Third, the proposed study will be somewhat protracted (no fewer than 4 weeks for each patient). Therefore, there is a risk of participant dropout, which could create a selection bias. We will try to alleviate dropout through monetary incentives for participation [85].

The proposed protocol will include a multi-facility, operator-blind, crossover randomised controlled trial to examine whether music therapy successfully reduces cannulation pain for dialysis patients. If predicted results manifest, we should have evidence that patients’ cannulation phobia and pain experiences can be reduced through a safe and cost-effective treatment strategy.

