### Study protocol

Figure 1 outlines the trial protocol and randomisation procedure. The intervention will be performed during each study period from the time of cannulation to the start of dialysis (thrice a week) (Table 1).

**Table 1 Tab1:** Summary of collected data at each time point according to SPIRIT 2013 guideline

TIME POINT	Enrolment HD1	1 week			1 week			1 week			1 week		
		HD2	HD3	HD4	HD5	HD6	HD7	HD8	HD9	HD10	HD11	HD12	HD13
ENROLMENT													
Eligibility screening	×												
Informed consent	×												
Allocation	×												
INTERVENTIONS													
Early-sequence													
No-sound		×	×	×				×	×	×			
Music					×	×	×						
White noise											×	×	×
Later-sequence													
No-sound		×	×	×				×	×	×			
Music											×	×	×
White noise					×	×	×						
ASSESSMENTS													
Baseline information	×												
VAS pain score		×	×	×	×	×	×	×	×	×	×	×	×
VAS anxiety score		×	×	×	×	×	×	×	×	×	×	×	×
STAI Y-1				×			×			×			×
STAI Y-2	×												
BP and HR		×	×	×	×	×	×	×	×	×	×	×	×
S-AMY				×			×			×			×
Conditional information		×	×	×	×	×	×	×	×	×	×	×	×
Adverse events		×	×	×	×	×	×	×	×	×	×	×	×

*Abbreviations*: *BP* blood pressure, *HD* haemodialysis, *HR* heart rate, *S-AMY* salivary amylase activity, *SPIRIT* Standard Protocol Items: Recommendations for Interventional Trials, *STAI* State-Trait Anxiety Inventory, *VAS* Visual Analogue Scale

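### The carry-over rule can switch the primary analysis to HD5–7 but states no use of the washout-week pain scores (HD8–10), which measure persistence more precisely than the weeks 2 and 4 totals

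*Protocol article*

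**What the plan says.** The Discussion of the protocol article acknowledges that carry-over could occur and answers it in two ways. The first is the design: "To minimise this possibility, we will implement a washout period (1 week) between the white noise and music periods". The second is a conditional rule: should carry-over emerge, the analysis will fall back on week 2 (HD5–7) as a parallel-group comparison, for which the sample size is said to be sufficient. No test, estimate, data source or threshold is given for deciding that carry-over has emerged.

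The primary analysis uses the two sound weeks only: "each patient will be assessed for six sets of the outcome variables (three in the music period and other three in the white noise period". These scores enter a linear mixed model with compound symmetry.

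The Design section puts both sequences in the no-sound condition in week 1 (run-in) and week 3 (washout). In Table 1 the row "VAS pain score" is marked at every session from HD2 to HD13, so it covers HD2–4 and HD8–10. The only stated use of the no-sound weeks is a secondary comparison of music and white noise with them (Discussion).

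**The concern.** The rule decides which analysis is primary and, when triggered, discards half of each patient's six scores. A rule of that weight should rest on the best available evidence. In week 3 the two randomised sequences differ only in the sound heard the week before, and each patient has a run-in score from before any exposure. The between-sequence difference in week 3 is therefore a randomised estimate of how far the effect persists into the washout. Nothing in the article connects these scores to the carry-over question.

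If carry-over is instead looked for within the six-score model, it appears only as a between-patient contrast of weeks 2 and 4 totals. That contrast is less precise and cannot be separated from a treatment-by-period interaction. A false alarm would cost the crossover comparison, and a real carry-over could be missed. Letting such a test select the analysis also inflates the type I error. The secondary comparison with no-sound is affected too, because using week 3 as a comparator assumes that no residual effect is left in it.

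**Working it through.** **The plan's own figure.** The Sample size section states "a difference of 4.9 mm was considered to be clinically significant and was used for the sample size design", that "the standard deviation was 12.0 mm", and that "we computed that 95 patients are needed to observe a treatment effect", at 80% power and two-sided 5%. The two-sample formula gives 2·12²·(1.96+0.84)²/4.9² ≈ 94.1, or 95 with the usual small-sample rounding. So 95 reproduces as a number per arm (190 in total). With 120 patients in total (60 per arm) and single-session scores, power for 4.9 mm is about 61%. This matters here because the fallback to HD5–7 is such a parallel comparison. Averaging three sessions or adjusting for run-in would raise the power, but the plan's calculation uses neither.

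**Inputs for the carry-over contrasts.** SD is 12 mm, taken as the SD of one session; the article does not say whether it is. There are 60 patients per sequence ("we will recruit a total of 120 participants", allocated equally). Compound symmetry is the plan's own covariance structure. The within-patient correlation r is not given, so it is assumed to be 0.4, 0.6 or 0.8.

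**Formulas.** The variance of a weekly mean is v = 144·(r + (1−r)/3). The covariance of two weekly means, or of one session with another week's mean, is c = 144·r. For a per-patient variance V, SE = √(2V/60), and the difference detectable with 80% power is 2.8·SE.

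- HD8–10 mean, adjusted for the HD2–4 mean: V = v − c²/v
- HD10 alone, adjusted for the HD2–4 mean: V = 144 − c²/v
- Weeks 2+4 total, unadjusted: V = 2v + 2c
- Weeks 2+4 total, adjusted for the HD2–4 mean: V = 2v + 2c − (2c)²/v

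In the weeks 2+4 total the treatment effects cancel between sequences. What is left is the carry-over difference in mm, so the rows below are on one scale.

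Example, r = 0.4: v = 86.4, c = 57.6, c²/v = 38.4. The four values of V are 48.0, 105.6, 288.0 and 134.4.

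| Contrast | SE (mm), r = 0.4 / 0.6 / 0.8 | Detectable (mm) |
|---|---|---|
| HD8–10, adjusted | 1.26 / 1.08 / 0.78 | 3.5 / 3.0 / 2.2 |
| HD10 alone, adjusted | 1.88 / 1.56 / 1.12 | 5.3 / 4.4 / 3.1 |
| Weeks 2+4, adjusted | 2.12 / 1.84 / 1.35 | 5.9 / 5.1 / 3.8 |
| Weeks 2+4, unadjusted | 3.10 / 3.58 / 4.00 | 8.7 / 10.0 / 11.2 |

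**Ratios of SE.** Weeks 2+4 against HD8–10 is about 1.7 with both adjusted and 1.8–2.0 with neither adjusted. Adjusted weeks 2+4 against adjusted HD10 alone is about 1.1–1.2. None of these ratios depends on the sample size or on the value of the SD. If 12 mm is the SD of a weekly mean, or if only 95 patients are analysable, all the mm figures rise together.

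**Effect of the switch.** I simulated the case with no treatment effect and no carry-over. The unadjusted weeks 2+4 test, at a 5% or 10% threshold, chose between the crossover comparison and week 2 alone. The overall type I error was about 8–9% instead of 5%.

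**The case against.** The strongest objection is that the article does not say how carry-over will be judged. Assessment methods usually sit in an analysis plan, and one may exist that is not shown. This stands as far as it goes. A reader might infer that the trial will test carry-over on weeks 2 and 4, but the text supports this only as the natural default of the six-score model. The absence of a detailed test would not be a finding. What remains is a rule that the article does fix, one that changes the primary analysis without saying what would trigger it.

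Three other readings are tempting and go too far.

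- **That the washout data are used only as a pooled comparator.** The Discussion gives the no-sound weeks a secondary comparison, but says neither that weeks 1 and 3 are pooled nor that this is their only use.
- **That the washout scores are 2.5–5 times as precise.** That comparison adjusts HD8–10 for run-in and leaves weeks 2+4 unadjusted, although the covariate is available to both. Like for like the ratio is about 1.7–2.0. With adjustment, weeks 2+4 would be informative, and it is not true that they say almost nothing.
- **That HD8–10 directly shows whether one week is long enough.** The bias in the crossover estimate comes from what remains at HD11–13. A difference at HD8 may be gone by then. HD10 is the most relevant session, and alone it is only slightly more precise than adjusted weeks 2+4. Contrast or treatment-by-period effects that arise only when the second sound is played cannot be seen in a no-sound week.

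**Conclusion.** The point holds in a limited form. HD8–10 pain scores are collected under identical conditions in both randomised sequences, with HD2–4 as baseline. The article states no use of them for carry-over, while fixing a rule under which carry-over changes the primary analysis. The adjusted HD8–10 contrast would detect persistence of about 2.2–3.5 mm, below the 4.9 mm design difference throughout the assumed range. The likely default would detect 3.8–5.9 mm with adjustment and 8.7–11.2 mm without. HD10 alone would detect about 3.1–5.3 mm.

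These figures rest on SD 12 mm per session, 60 patients per sequence, compound symmetry and an assumed correlation of 0.4–0.8. The inflation to about 8–9% applies only if the usual unadjusted weeks 2+4 test is what triggers the switch. The change should be made: it is cheap, and it removes a data-driven choice of primary analysis.

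**What to change.** 1. State that persistence during washout will be reported as the between-sequence difference in mean HD8–10 VAS pain, adjusted for mean HD2–4 VAS pain, with a 95% CI. Show HD8, HD9 and HD10 separately, with HD10 as the most relevant.
2. State that this result serves only to interpret the crossover estimate and the secondary comparison with no-sound, and does not choose the analysis.
3. Replace the conditional switch in the Discussion: the crossover analysis stays primary whatever the check shows, and the HD5–7 parallel comparison is always reported as a sensitivity analysis.
4. Note that the check cannot detect contrast or treatment-by-period effects that appear only with the second sound.

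The cost is one extra model and a change of wording, with no new data or visits. The article plans no interim analysis, so the change can still be prespecified if it is fixed before outcomes are examined by sequence.
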